6.5.2.8 Protocol visit #7: Stage 2, end of IFN- $\gamma$  therapy assessment

- At the 12 weeks (+/- 2 weeks) after the first dose of IFN- $\gamma$
- Clinical safety monitoring: Any reaction or symptoms related to the IFN- $\gamma$  or DLI will be assessed, specifically focusing on active grade II-IV GVHD or de novo grade III-IV, or progressive chronic GVHD
- Laboratory monitoring: CBC with differential, chemistry panel (Na, K, Cl, CO2, creatinine, glucose, urea nitrogen, phosphorus, magnesium, albumin, calcium, LDH, uric acid), hepatic (alkaline phosphatase, ALT, AST, and total bilirubin) panel
- STR chimerism of bone marrow (if available) and peripheral blood (CD3 and myeloid)
- **Bone marrow aspirates** will be performed for morphology, flow cytometry, and research sample (10mL). Cytogenetics/molecular testing only needed if clinically indicated to follow MRD within 2 weeks after the last dose of IFN- $\gamma$

- Research sample collection: 10mL of bone marrow (10ml green top heparin tube), 30 mL of peripheral blood (10 mL green top heparin tube x 3 tubes) will be collected.
- The date of the last dose of IFN- $\gamma$  will be recorded.

6.5.2.9 Protocol visit #8: 28 days (+/- 2 weeks) safety assessment after the last dose of IFN- $\gamma$  therapy (Off treatment assessment)

- Clinical safety monitoring: Any reaction or symptoms related to the IFN- $\gamma$  or DLI will be assessed, specifically focusing on active grade II-IV GVHD or de novo grade III-IV, or progressive chronic GVHD. Monitoring of adverse events annotated to IFN- $\gamma$  therapy will be completed on this off-treatment assessment visit
- Laboratory monitoring: CBC with differential, chemistry panel (Na, K, Cl, CO2, creatinine, glucose, urea nitrogen, phosphorus, magnesium, albumin, calcium, LDH, uric acid), hepatic (alkaline phosphatase, ALT, AST, and total bilirubin) panel
- Research sample collection: 30 mL of peripheral blood (10 mL green top heparin tube x 3 tubes) will be collected.

6.5.2.10 Protocol visit #9: Off study assessment: 6 months (+/- 4 weeks) after the first dose of IFN- $\gamma$

- Clinical outcome monitoring: Any reaction or symptoms related to the IFN- $\gamma$  or DLI will be assessed, specifically focusing on active grade II-IV GVHD or de novo grade III-IV, or progressive chronic GVHD. Other clinical outcomes, including the latest disease status, will be recorded.
- STR chimerism of peripheral blood (CD3 and myeloid)
- Optional bone marrow aspirates (no biopsy) will be performed for morphology, flow cytometry, and research sample (10ml). Cytogenetics/molecular testing only needed if clinically indicated to follow MRD if clinically indicated.
- Research sample collection: 10ml of bone marrow (green top heparin tube) if collected, 30 mL of peripheral blood (10 mL green top heparin tube x 3 tubes) will be collected.

## 6.6 Management of Complications

### 6.6.1 Criteria for Dose Reduction of IFN- $\gamma$

The dose of IFN- $\gamma$  will be reduced when the subject is considered to have an intolerance to IFN- $\gamma$  defined by the following criteria.

#### 6.6.1.1 Graft versus host disease

- De novo grade II GVHD
- Progressive chronic GVHD requiring new systemic treatment or increased doses of current systemic treatment
- Any grade of GVHD which requires increased doses of current treatment per treating physician's determination

#### 6.6.1.2 Other organ diseases

- New onset of seizure which is not medically controlled

- New onset of cardiac ischemia, congestive heart failure or arrhythmia which is not medically controlled
- New onset of grade 3 or greater AST or ALT elevation
- Development of acute kidney failure with an estimated GFR < 30 mL/min

#### 6.6.1.3 Intolerance per the subject

- If the subject develops intolerance due to the expected adverse events (listed in Section 9.2.2), the dose may be reduced per treating physician or investigator discretion. If the symptoms are eventually attributed to other cause or resolve, then the dose may be increased again, per treating physician or investigator discretion.

### 6.7 Criteria for Discontinuation of IFN- $\gamma$

Specific conditions that will require discontinuation of IFN- $\gamma$  are as follows:

- Pregnancy
- New-onset grade 3 or 4 acute GVHD
- Progression of disease which requires immediate cytoreduction chemotherapy or other therapy per treating physician's determination
- Immediate hypersensitivity reaction associated with a study injection
- Intercurrent CTCAE grade 3 or 4 illness or organ dysfunction (other than cytopenias and electrolyte abnormalities) that does not resolve to grade  $\leq$  1 within two weeks
- The study site PI or treating physician assesses that it is not in the best interest of the subject to continue on the study.
- The dose of IFN- $\gamma$  can be discontinued anytime based on the clinical status of the subject at the treating physician's discretion. If IFN- $\gamma$  is not given for six doses, the subject will be withdrawn from further on-study treatment.

### 6.8 Management of hypersensitivity reactions to IFN- $\gamma$

If a systemic hypersensitivity reaction occurs, IFN- $\gamma$  should be discontinued immediately and appropriate medical therapy should be instituted. For a severe hypersensitivity reaction, intramuscular epinephrine and intravenous antihistamines and systemic steroid with fluid resuscitation should be immediately initiated under appropriate clinical monitoring.

### 6.9 Management of Other Complications

- 6.9.1 Cytopenia, GVHD, and infection: Management of cytopenia, GVHD, and infection will be per the institutional Standard Practice Guidelines. These complications could be due in part or in full to IFN- $\gamma$ , DLI, or the side effects of the transplant itself.

### 6.9.2 Flu-like symptoms

Flu-like symptoms such as fever, chills, rash, headache, myalgia, tachycardia, shortness of breath, nausea, and diarrhea can occur especially within the first week of IFN- $\gamma$  treatment. Treatment for flu-like symptoms will be primary supportive (i.e., empiric antibiotics, IV fluid, antipyretic, anti-emesis, anti-diarrheal after ruling out infectious causes). Some of “flu-like” symptoms may be minimized by bedtime administration of IFN- $\gamma$ . Prophylactic acetaminophen may also be used to ameliorate these effects.

### 6.9.3 Organ failure

- Neurologic: Decreased mental status, gait disturbance, and dizziness have been observed, particularly in patients receiving IFN doses greater than 250 mcg/m^2/day (greater than 10 times the weekly maximal dose in this study). Most of these abnormalities were reversible within a few days upon dose reduction or discontinuation of therapy. We will clinically monitor the patients with seizure disorders or compromised central nervous system function.
- Cardiopulmonary system: Patients with pre-existing cardiopulmonary conditions, including ischemia, congestive heart failure, or arrhythmia, will be clinically monitored for signs/symptoms of exacerbation. Some of “flu-like” symptoms may be minimized by bedtime administration of IFN- $\gamma$ . Acetaminophen may also be used to ameliorate these effects.
- Liver: Repeated administration of IFN- $\gamma$  to patients with advanced hepatic disease may result in accumulation of interferon gamma-1b. Elevations of aspartate transaminase (AST) and/or alanine transaminase (ALT) (up to 25-fold) have been observed during IFN- $\gamma$  therapy. The transaminase elevations were reversible with reduction in dosage or interruption of IFN- $\gamma$  treatment. If severe hepatic enzyme elevations develop, IFN- $\gamma$  dosage will be modified according to the dose reduction criteria described in section 6.
- Renal: Renal toxicity has been reported in patients receiving IFN- $\gamma$ ; if new or progressive renal insufficiency occurs, that cannot be attributed to another cause (for example, a nephrotoxic medication), the dosage will be modified according to the dose reduction criteria described in section 6.6.1. Nephrology consultation is recommended in this case.

## 6.10 Collection of Biospecimens

### 6.10.1 Saliva collection (optional)

The subject will be provided with a saliva collection kit and instructed to collect the saliva according to manufacturing instruction. Saliva collection can be repeated one more time if the amount of extracted DNA is not adequate for subsequent sequencing. Collection of saliva can occur at any time during the study.

### 6.10.2 Bone marrow aspirates

- An extra volume (goals of a minimum of 5 mL, up to 10 mL) of bone marrow aspirate will be collected for research at the specific time point, as described in section 6.5.

### 6.10.3 Peripheral blood collection

- Peripheral blood will be collected from the subjects, as described in section 6.5. The volumes of blood collection 30 mL of peripheral blood per time point. The research blood draw will not be performed when the hemoglobin level is less than 7.5 g/dL.

## 6.11 Biospecimen Management and Research Data Collection

6.11.1 De-identification of the biospecimen: each biospecimen will be assigned a de-identified accession number according to the standard operating procedure at Hillman Cancer Center Research Pavilion Lab 1.33.

## 7. LABORATORY RESEARCH STUDIES

### 7.1 Response of malignant blasts to IFN- $\gamma$

Using flow cytometry, we plan to measure the IFN- $\gamma$  response of malignant blasts through phosphorylated STAT1 (pSTAT1), a canonical pathway of IFN- $\gamma$  receptor (IFN- $\gamma$ R) and surface expressions of other IFN- $\gamma$  inducible molecules such as HLA-class I, HLA-class II, ICAM-1. We will also perform single-cell RNA sequencing (sc-RNAseq), or bulk RNA sequencing (RNAseq) of malignant blasts pre and post in vivo IFN- $\gamma$  therapy, to identify IFN- $\gamma$ -induced transcriptional changes.

### 7.2 Cellular and humoral immune response to IFN- $\gamma$

We also plan to analyze the immune response to IFN- $\gamma$  by analyzing T-cell subset with flow

phenotype using spectral analyzer (Cytek™ Aurora) which includes markers of memory subset (CD45RO, CCR7), regulatory T cells (CD25hi CD127lowFoxP3+), activation and exhaustion (PD1, LAG3, Tim3, and TIGIT). We will measure plasma IFN-γ and related cytokines (IP-10) using a multiplex ELISA panel. Antigen-specific T cells against infectious pathogens (i.e., CMV or EBV) or minor histocompatibility antigens (miHAs, such as HA-1) may also be assessed.

## **8. STATISTICAL CONSIDERATIONS**

### **8.1 Study Endpoint**

#### **8.1.1 Primary safety endpoint:**

To evaluate the adverse events of IFN-γ in relapsed patients after alloSCT, per CTCAE v5.0

To evaluate the adverse events of IFN-γ in relapsed patients after alloSCT with concurrent use of donor lymphocyte infusion, per CTCAE v5.0

##### **8.1.1.1 Analysis plan**

Adverse events will be summarized via descriptive statistics. The maximum grade of toxicity for each category of interest will be recorded for each patient and the summary results will be tabulated by category and grade.

The following data will be reported

- Incidence of graft-versus-host disease (GVHD) progression
- Incidence of de novo GVHD
- Incidence of serious adverse events (SAE) or grade 3 or 4 unexpected, suspected adverse reaction defined in section 9.1

#### **8.1.2 Primary biological endpoint:**

Upregulation of key targets including HLA-ABC and -DR/DQ, ICAM-1 and generation of phosphorylated STAT1 (pSTAT1) in bone marrow malignant blasts post-IFN-γ treatment, measured by the changes in mean fluorescent intensity and percentage of positive cells by flow cytometry

##### **8.1.2.1 Analysis plan**

Biological parameter measurements and outcomes will be presented via descriptive statistics, table or figure.

### **8.2 Sample Size**

#### **8.2.1 Sample Size:**

Our goal is to have at least three patients complete intra-subject dose escalation and receive at

least one dose of DLI. We anticipate enrolling 6 total patients and likely no more than 9 as some patients may not be able to complete the study due to rapid disease progression or the unavailability of DLI.

For cohort 2, we aim to enroll at least three patients receiving IFN- $\gamma$  and at least one dose of DLI. We anticipate enrolling up to 6 patients as some patients may not be able to complete the study due to rapid disease progression.

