Cohort 2: As we confirmed the safety of IFN- $\gamma$  monotherapy in the first cohort, we will evaluate a second cohort wherein we will shorten IFN- $\gamma$  monotherapy (stage 1) to 1 week before DLI. In stage 1, we will assess the safety a fixed-dose of IFN- $\gamma$  (100mcg subcutaneously three times per week) for one week. The bone marrow biopsies will be performed before and no earlier than 48 hours to 1 week after the first dose of IFN- $\gamma$  to assess malignant blasts for an IFN- $\gamma$  response. In stage 2, subjects who have tolerated IFN- $\gamma$  will receive DLI in a dose-escalating manner. IFN- $\gamma$  will be continued three times a week for seven weeks after the first dose of DLI, followed by once-weekly IFN- $\gamma$  for four weeks. The patients will be off treatment after a 12 week-course of IFN- $\gamma$  with a repeat bone marrow biopsy at this point. The clinical outcomes will be monitored at six months after the first dose of IFN- $\gamma$  and then the subjects will be off study. Figure 2 summarizes the study design for cohort 2.

Sample size: Our goal is to have at least three patients receive at least one dose of DLI. For example, if the first three patients all complete stage 1 and stage 2, this initial pilot study would be completed with three patients. We estimate enrolling six total patients, but not likely more than nine, as some patients may not be able to complete the study due to the development of rapid disease progression or unavailability of DLI. Based on the nature of the transplant populations at our centers, we estimate accrual will be completed within six months.

For cohort 2, we aim to enroll six patients receiving IFN- $\gamma$  and at least one dose of DLI.

[figure not shown]

**Figure 1. Study Design of Cohort 1:** The figure outlines the scheme of how to administer IFN- $\gamma$  and subsequent donor lymphocyte infusions after enrollment. Biospecimens will also be collected, as shown. BM: bone marrow aspirates, DLI: donor lymphocyte infusion, IFN- $\gamma$ : interferon-gamma, PBMC: peripheral blood mononuclear cells

[figure not shown]

**Figure 2. Study Design of Cohort 2:** The figure outlines the scheme of how to administer IFN- $\gamma$  and subsequent donor lymphocyte infusions after enrollment. Biospecimens will also be collected, as shown. BM: bone marrow aspirates, DLI: donor lymphocyte infusion, IFN- $\gamma$ : interferon-gamma, PBMC: peripheral blood mononuclear cells

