### 8.2.2 Accrual Rate

We plan to accrue six to nine subjects during the first six months and complete the study in one year.

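### The cohort 2 target is six DLI-treated patients in the synopsis but at least three, from up to six enrolled, in Section 8.2.1; the cohort 1 target and the accrual statement also need aligning

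*Protocol*

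**What the plan says.** **Cohort 2.** The Sample size paragraph of the synopsis states: "For cohort 2, we aim to enroll six patients receiving" IFN-γ and one or more DLIs. Section 8.2.1 states: "we aim to enroll at least three patients receiving" IFN-γ and one or more DLIs. It then adds: "We anticipate enrolling up to 6 patients as some patients may not be able to complete the study due to rapid disease progression".

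**Cohort 1.** The synopsis states: "Our goal is to have at least three patients receive at least one dose of DLI". Section 8.2.1 asks that "at least three patients complete intra-subject dose escalation" and also receive one or more DLIs. Both places forecast six enrolled and probably not more than nine.

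**Accrual.** Section 8.2.2 states: "We plan to accrue six to nine subjects during the first six months and complete the study in one year".

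**Dosing.** Sections 2.2 and 6.3.2 give IFN-γ as a flat 100 mcg per injection, three injections a week, with planned changes only towards fewer injections. Section 6.6.1.3 allows a discretionary return after an earlier reduction. DLI is the component that rises within a patient: Table 3 in Section 6.4.1.3 lists increasing cell doses from the first to the third infusion, with the actual dose left to the treating physician.

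**The concern.** Both cohort 2 statements count the same thing, patients given IFN-γ together with DLI, and one number is twice the other. They cannot be explained as enrolled versus treated. The synopsis attaches six to treated patients, while Section 8.2.1 uses six as the enrolment figure precisely because not everyone enrolled is expected to complete.

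This number is the denominator for a primary safety endpoint, adverse events of IFN-γ with concurrent DLI (Sections 1.1.3.2 and 8.1.1). If it is undefined, the protocol does not say when cohort 2 has met its goal or how much safety information on the combination it is meant to deliver.

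Two related statements are also out of line. The cohort 1 target in Section 8.2.1 carries a condition that is absent from the synopsis and does not fit the treatment plan, and the accrual and duration statement does not appear to include cohort 2.

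**Working it through.** **No calculation to reproduce.** The protocol gives no error rate, effect size, precision target or numeric dropout rate for its sample size. The check compares the stated figures and shows what the difference means.

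**1. Cohort 2 targets.** Synopsis: 6 treated. Section 8.2.1: at least 3 treated, up to 6 enrolled, some not completing. With 6 enrolled and a share q reaching DLI, the expected number treated is 6q, which is below 6 for any q below 1.

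**2. Chance of reaching each target from six enrolled.** The protocol does not state q, so the values below are assumptions. With X binomial(6, q), P(X = 6) = q⁶ and P(X ≥ 3) is the upper tail. The enrolment needed on average for a target k is k/q, rounded up.

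| Assumed q | P(all 6 treated) | P(at least 3 treated) | Enrolment for 6 treated | Enrolment for 3 treated |
|---|---|---|---|---|
| 0.50 | 0.50⁶ = 1.6% | 66% | 12 | 6 |
| 0.75 | 0.75⁶ = 18% | 96% | 8 | 4 |
| 0.90 | 0.90⁶ = 53% | 99.9% | 7 | 4 |

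An enrolment of six therefore suits a target of three over much of this range. It suits a target of six only if almost nobody is lost.

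**3. Precision of the combination safety data.** With zero events in n patients, the one-sided 95% upper bound is 1 − 0.05^(1/n).
- n = 3: 1 − 0.05^(1/3) = 0.632, or 63%.
- n = 6: 1 − 0.05^(1/6) = 0.393, or 39%.

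For a toxicity with an assumed true rate of 20%, the chance of seeing at least one case is 1 − 0.8ⁿ: 0.49 at n = 3 and 0.74 at n = 6.

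**4. Cohort 1 wording, on either reading.**
- If the escalation means IFN-γ, none is planned: the dose is flat and scheduled adjustments go downward. A discretionary return after a reduction is not an escalation to be completed.
- If it means DLI, the dose first rises at the second infusion in Table 3, so completing it takes at least two infusions. The same sentence and the synopsis ask for only one.

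Both readings conflict with the synopsis goal.

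**5. Accrual.** Six to nine subjects is the cohort 1 forecast alone. Adding up to six for cohort 2 gives at most 9 + 6 = 15. Six months of accrual plus six months of follow-up per patient (Section 6.5.1.10) already uses the one year for cohort 1. Cohort 2 comes after cohort 1 safety has been confirmed (synopsis) and has its own six-month visit (Section 6.5.2.10).

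**The case against.** The best defence is that these are stated as aims and forecasts in a descriptive pilot. Three is a floor, six satisfies it, and the enrolment figure is an expectation rather than a hard cap. No test, error rate or decision threshold depends on cohort size, so power and type I error are untouched. Taken alone, Section 8.2.1 is workable: at an assumed 75% yield, six enrolled gives a 96% chance of at least three treated.

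All of that stands, but it does not reconcile the two sections. A plan to treat six and a plan to treat at least three from about six enrolled with losses are different plans, and nothing in the protocol says which governs.

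Four stronger readings are tempting and should not be drawn:

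- **That no dose escalation exists in the trial, so no cohort 1 patient could qualify.** DLI does escalate within a patient. Only an IFN-γ escalation is absent.
- **That the protocol implies a DLI yield of 33% to 50%, from three treated among six to nine enrolled.** That divides a minimum goal by an enrolment forecast. The synopsis says the pilot could finish with three patients if the first three complete. Cohort 1 losses also include lack of DLI, whereas the cohort 2 sentence names only rapid progression, so the ratio would not carry over.
- **That closing cohort 2 at three or six would be decided after seeing results.** Nothing in the protocol indicates this. Finishing at three is illustrated only for the initial pilot.
- **That this target is the only rule that can stop the cohort.** Section 8.4 provides for suspension, and Section 13 gives the monitoring bodies authority to suspend accrual.

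**Conclusion.** The contradiction is real and can be read directly from the text: six against at least three for the same unit, with an enrolment figure that reaches six only with no attrition. It concerns the denominator of a primary safety endpoint. Its effect is limited to when cohort 2 is complete and how precise its safety data are: a zero-event upper bound of 63% or 39%, depending on which number applies. Those bounds follow from n alone. The probabilities of reaching each target rest on assumed yields of 50% to 90%, but the mismatch exists at any yield below 100%.

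The cohort 1 condition in Section 8.2.1 disagrees with the synopsis on either reading of the escalation. The accrual statement matches cohort 1 alone; that is a smaller matter with no effect on the analysis. The documents do not show which cohort 2 number is intended, so the sponsor must decide.

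**What to change.** - State one cohort 2 target, counted in DLI-treated patients, identically in the synopsis and Section 8.2.1. Give with it an enrolment ceiling that allows for the expected attrition, and name the yield assumed.
- Reconcile the cohort 1 target in Section 8.2.1 with the synopsis goal of at least three patients given one or more DLIs, so that the escalation condition no longer conflicts with it.
- Restate number, accrual period and duration in Section 8.2.2 for both cohorts together.

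The cost is a text amendment to three places. If three is the intended target, no patients are added, but the safety data are stated with the wider bound (63% rather than 39%). If six is intended, the enrolment figure has to rise: to 8 at an assumed 75% yield, or 12 at 50%.

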### 8.2.2 Accrual Rate

We plan to accrue six to nine subjects during the first six months and complete the study in one year.

## 8.3 Off Study Criteria

### 8.3.1 Completion of study

Following the completion of IFN- $\gamma$  and off treatment monitoring period, the subjects will have completed protocol participation and will be considered off study at the off-protocol visit, defined in section 6.5

### 8.3.2 Criteria for removal of a subject from the study

Subjects may be removed from the study, as described below. Subjects that are removed will have a final “off study” visit. If such subjects had bone marrow aspirates before and after IFN- $\gamma$  (i.e., Protocol Visit #2), data from those aspirates will be included in assessing the biological endpoint.

- The subject does not receive at least 2 doses of IFN- $\gamma$  per week due to noncompliance.
- The subject develops a medical condition that is a contraindication to IFN- $\gamma$  as described in Section 6.7, Criteria for Discontinuation of IFN- $\gamma$ , without having already received at least 4 weeks of IFN- $\gamma$  therapy.
- The subject becomes pregnant.
- The study PI assesses that it is not in the best interests of the subject to continue participation in the study or that the subject is not compliant with the investigation.

